CST was originally developed from a Cochrane systematic review of psychological interventions for people with dementia^8^ and has been shown to be cost-effective, to improve quality of life and to enhance cognition to an extent comparable with trials of cholinesterase inhibitors.^5–7^ CST is based on the principle that stimulating engagement in cognitive and social activity enhances cognitive function and quality of life. However, in spite of the success of the therapy in a group setting, it was recognised that not all people with dementia may have access to, or wish to participate in, group activities. CST was therefore adapted for home-based individualised administration (via a study companion) in the form of ‘individual CST’ (iCST).^5^

The efficacy of iCST was recently investigated in a 26-week multicentre, single-blind, randomised controlled trial (RCT).^5^ The findings revealed a significant improvement in the quality of the relationship of the person with dementia and their study companion, as well as an improvement in health-related quality of life for companions (designated ‘caregivers’). Furthermore, iCST was found to be feasible for people who found travel a barrier to participation. Outcomes related to those who support or care are particularly important, since the perceived burden of care has been shown to be significantly related to the extent of associated cognitive impairment in the person living with Parkinson's-related dementia.^9^ This may be in part due to the added responsibility of managing the impact of concurrent cognitive, psychiatric and physical impairments in the cognitively impaired person. Nonetheless, in spite of the positive findings mentioned above, iCST did not appear to improve cognition or quality of life of the cognitively impaired participants themselves.

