## Methods

This protocol was prepared in accordance with SPIRIT 2013 statement^12^ (checklist is available as an online supplementary file). The trial is registered with the ISRCNT (ISRCTN11455062); all study-related items from the WHO Trial Registration Data Set are available at the registry. The protocol lies within a research programme comprising a series of sequential steps in the development, feasibility testing, piloting and eventual full-scale trialling of a complex psychosocial intervention for people with PDD, MCI-PD or DLB. The programme has followed the UK's MRC's updated Guidance on ‘Developing and Evaluating Complex Interventions^10^ and is now at the feasibility, exploratory and pilot trial stage, which we describe here. Specifically, this part of the programme is a fully controlled randomised single-blind exploratory pilot trial with an embedded feasibility process evaluation and evaluation of new outcomes. The protocol for the process evaluation is not reported here but will form the basis of other papers. The pilot trial is designed and powered to test the hypothesis that CST-PD is superior to TAU for people with PDD, MCI-PD or DLB in improving cognitive function when assessed at baseline and 12 weeks post-randomisation. The therapy will be delivered in participants’ homes with recruiting sites in locations in Greater Manchester and other regions in the UK. A CONSORT-style flow chart for the trial is shown in figure 1.

10.1136/bmjopen-2017-016801.supp1Supplementary material 1

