### Sample size

A predetermined sample size for the feasibility aspects of this study is not required, since inferential statistics will only be exploratory. The sample size is determined by that required to detect a clinical meaningful difference in our primary outcome measure, cognitive function. To determine sample size, we referred to the previous literature^7 8 16^ and, taking a conservative approach, have estimated the standardised effect size on cognition of the parent form of the intervention to be 0.4. Thus, assuming 80% power and a correlation coefficient of 0.5 between baseline and endpoint on cognitive outcomes, the required sample size is 27 completers per group. By enrolling 32 dyads per group, it will allow for a 15% attrition rate (consistent with pilot sample guidance^17^). For the secondary, exploratory outcomes, the proposed sample size of 27 per group is within the recommended guidelines (24–50 participants^18 19^) required to estimate the standard deviation (SD) for a sample size calculation.

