### Summary

This mixed-methods protocol describes an early phase trial designed to primarily evaluate the feasibility and acceptability of CST-PD and whether there is sufficient evidence of clinical efficacy to justify a subsequent larger RCT. The protocol is congruent with the UK's MRC's updated guidance on ‘Developing and Evaluating Complex Interventions’^10^ and serves to enhance the design of a subsequent definitive large-scale trial.

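### The stated inputs (effect 0.4, correlation 0.5, 80% power) do not give 27 completers per group under either planned test at a conventional significance level

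*Protocol article*

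**What the plan says.** The Sample size section of the protocol article derives the trial's size from cognition. For the effect, the authors, "taking a conservative approach, have estimated the standardised effect size on cognition of the parent form of the intervention to be 0.4". The section continues: "assuming 80% power and a correlation coefficient of 0.5 between baseline and endpoint on cognitive outcomes, the required sample size is 27 completers per group". Enrolment is then raised to 32 dyads per group for 15% attrition. No significance level or sidedness is given. The same section adds a second justification for the exploratory outcomes: 27 per group lies within a cited guideline of 24 to 50 participants for estimating an SD.

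Primary and exploratory outcome measures gives the test as a between-group comparison of change, by t-test or by analysis of covariance adjusting for baseline differences. The hypothesis is directional: a greater change in the CST-PD arm.

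The claim of adequate power recurs. The opening of Methods says: "The pilot trial is designed and powered to test the hypothesis that CST-PD is superior to TAU". Table 1 (row on number and variability of outcomes), the section on the control group, and Primary and exploratory outcome measures say the same in other words. The Summary says that the trial will assess feasibility and acceptability first, and also "whether there is sufficient evidence of clinical efficacy to justify a subsequent larger RCT".

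**The concern.** The article prints both the inputs of a power calculation and its result, so the result can be checked, and it does not follow from them. A correlation of 0.5 gives no gain in precision for a change score and only a modest gain for ANCOVA. An effect of 0.4 SD would normally call for several times 27 per group.

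What is at stake is how the efficacy result is read. Someone told that the trial had 80% power for 0.4 SD will take a non-significant difference as fairly strong evidence against an effect of that size. At the power the inputs imply, it would be weak evidence. Table 1 adds to this: it presents training fidelity as a way to keep a non-significant result from being put down to poor training instead of an ineffective therapy.

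**Working it through.** **Inputs from the protocol.** Effect d = 0.4, correlation r = 0.5, power 80% and n = 27 completers per group in two equal arms (Sample size). Test: t-test on change or ANCOVA (Primary and exploratory outcome measures).

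**Assumptions.** d is a between-group difference in units of the cross-sectional SD. The level is not stated, so two-sided 5% and one-sided 5% are both shown.

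**Step 1: the attrition step.** 27 / (1 − 0.15) = 31.8, rounded up to 32. This reproduces. The problem lies in the 27.

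**Step 2: SD of the analysed quantity, with raw SD = 1.**
- Change score: √(2(1 − r)) = √(2 × 0.5) = 1.00
- ANCOVA residual: √(1 − r²) = √0.75 = 0.866

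**Step 3: completers needed for 80% power.** The normal approximation is n = 2 s² (z_α + z_β)² / d² per group, with z_β = 0.842.
- Change, two-sided 5%: 2 × 1.00 × (1.960 + 0.842)² / 0.16 = 98.1, so 99
- ANCOVA, two-sided 5%: 2 × 0.75 × (1.960 + 0.842)² / 0.16 = 73.6, so 74
- Change, one-sided 5%: 2 × 1.00 × (1.645 + 0.842)² / 0.16 = 77.3, so 78
- ANCOVA, one-sided 5%: 2 × 0.75 × (1.645 + 0.842)² / 0.16 = 58.0, so 58

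The exact noncentral t gives 100, 75, 78 and 59. None is near 27.

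**Step 4: power at 27 per group for d = 0.4.** The noncentrality is d / (s√(2/27)): 0.4 / 0.272 = 1.47 for change and 0.4 / 0.236 = 1.70 for ANCOVA. Exact noncentral t:

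| Level | t-test on change | ANCOVA |
|---|---|---|
| two-sided 5% | 30% | 38% |
| one-sided 5% | 42% | 51% |
| one-sided 10% | 57% | 66% |

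If all 32 per group completed, power at two-sided 5% would be 35% or 44%.

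**Step 5: what level would make 27 correct?** The critical value must be about the noncentrality minus 0.842.
- ANCOVA: 1.70 − 0.84 = 0.86, a one-sided level of about 0.20. The exact n at 0.20 is 27.
- t-test on change: 1.47 − 0.84 = 0.63, a one-sided level of about 0.27.

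The protocol states neither.

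**Step 6: what 27 per group delivers at two-sided 5%.**
- Effect detectable with 80% power: 0.78 SD (change) or 0.67 SD (ANCOVA).
- 95% CI half-width, t(0.975) × s√(2/27): 2.007 × 0.272 = 0.55 SD, or 2.007 × 0.236 = 0.47 SD.

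**The case against.** **The level is unstated and the hypothesis is directional.** This stands in part. Power of 30% to 38% cannot be given as fact; across the two tests at 5%, one-sided or two-sided, the range is about 30% to 51%. No conventional choice reaches 80%.

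**The true correlation may exceed 0.5.** It may. With ANCOVA at two-sided 5%, r = 0.8 would give 67% power and r = 0.85 would give 78%. But the printed calculation fixes r at 0.5. The point is an inconsistency among stated inputs, not a claim to know the trial's real power.

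**This is a pilot, and the text is cautious.** Objectives puts feasibility and process first and makes efficacy a secondary exploration. Primary and exploratory outcome measures promises cautious interpretation. Both soften the consequence. However, the reasons given for caution are the adapted therapy and the single outcome measure, not low power, and the same passage keeps the claim that the trial is powered.

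**The size is defensible on other grounds.** This stands. The 24 to 50 guideline for estimating an SD is untouched by the error.

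**Stronger readings that the documents do not support.**
- A reader might infer that 0.4 is not a conservative choice, because the Background reports that "iCST did not appear to improve cognition or quality of life of the cognitively impaired participants themselves". But the word is applied to the estimate for the parent therapy, drawn from cited sources that cannot be checked here. The iCST result is disclosed, and the need for adaptation is explained.
- A reader might infer that a null result would end the programme. No significance-based stop or progression rule is set anywhere.
- How 27 was obtained is not documented, and nothing here depends on guessing it.

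**Conclusion.** The sample-size statement is wrong as written: its inputs and its result do not agree under either named test at any conventional significance level. At two-sided 5% the required number is 2.8 times (ANCOVA, 75 / 27) to 3.7 times (t-test on change, 100 / 27) the stated one. At one-sided 5% it is 2.2 to 2.9 times (59 / 27 and 78 / 27). A true effect of 0.4 SD would be missed in roughly half to 70% of such trials, depending on the level and the test. The claims of being powered on cognition lose their basis. The 32 dyads per group do not, because the SD-estimation purpose supports them. The conclusion rests on reading 0.4 as a between-group standardised difference and on the stated correlation of 0.5.

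**What to change.** Keep 32 dyads per group and correct the text.

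1. In Sample size, state the significance level, the sidedness and which of the two tests is primary, and restate the figure for that choice. For example, at two-sided 5%, 27 completers per group give about 38% power for 0.4 SD by ANCOVA (30% by t-test on change), 80% power for about 0.67 SD (0.78 SD), and a 95% CI half-width of about 0.47 SD (0.55 SD). If a level near one-sided 0.20 was intended, say so and justify it.
2. Withdraw or qualify the claims that the trial is powered on cognition in the opening of Methods, Table 1, the control-group section, and Primary and exploratory outcome measures.
3. Rest the sample size on the SD-estimation guideline already cited.
4. Report the cognitive effect as an estimate with its 95% CI. In the Summary, say that a non-significant result will not be read as evidence of no effect when judging whether a larger RCT is justified.

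The cost is wording only: no extra dyads, assessments or time. The stated power becomes less favourable, and the efficacy aim becomes one of estimation.

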### Randomisation and blinding

Eligible dyads will be identified at recruiting centres by trial collaborators (principal investigators) and research nurses and therapists. Participant and companion information sheets outlining the study objectives, risks and benefits will be shared with each dyad. Informed consent from the participant and companion, based on the Good Clinical Practices guidelines published by International Council for Harmonisation,^20^ will be gained during the home screening visit (participant and companion information sheets and informed consent forms are available as on online supplementary file). In line with the aforementioned iCST/CST trials, guidance from the British Psychological Society on evaluation of capacity will be followed. In the event of a participant with PDD/DLB not having capacity at study entry or losing capacity after study entry, the ethics committee has approved the INVEST trial implementer to gain consent from an acceptable, nominated representative. During the home screening, the unblinded trial implementer will administer the Montreal Cognitive Assessment (MoCA)^21^ and Schwab and England Activities of Daily Living Scale^22^ to confirm eligibility and collect demographic data. Once the participant and companion are consented, blinded assessors will conduct baseline assessments in the dyad's home.

Following baseline assessment, the unblinded trial implementer will randomise the dyad to one of two arms: CST-PD or TAU. A tamper proof process of single-strata, blocked randomisation will be applied and communicated via telephone and confirmatory email by an independent arbiter, the Manchester Academic Health Science Centre Clinical Trials Unit. Due to the nature of the intervention, dyads will not be blind to treatment allocation.

Immediately following the intervention period (see below for details), the blinded assessors will visit dyads in their home to conduct post-test assessments. The unblind trial implementer will remind all dyads to maintain the blind during the assessment. Following assessment, blinded assessors will be asked to record the arm to which they believed the dyad was allocated to.

### Active intervention

The active intervention, CST-PD, is based on conventional CST^7^ and iCST^5^ and was developed by means of an iterative process involving significant user, companion and professional input. This adaptation process is described in detail elsewhere and has resulted in a condition-specific cognitive stimulation therapy manual with training guidance. The manual comprises over 60 topics categorised into nine different themes (table 3). Each topic contains several cognitively stimulating activities, for example, discussion suggestions, word association and creative tasks. Activities vary in complexity and can be matched and adapted to suit the needs of the participant. It is recommended that the companion-guided therapy is delivered in 30 min sessions, three times a week over 10 weeks.

**Table 3 T3:** Themes and sample topics from the CST-PD manual

Session theme	Sample topics
Personal life	Childhood, family, relationships
Food	World cuisine, staying healthy, ingredients
Hobbies and leisure	My perfect day, pets, gardening
Art	History of art, Lowry and Turner, architecture
Media and entertainment	Musical instruments, current affairs, technology
Nature	Weather, water, animal kingdom
Seasons	Spring, Summer, Autumn, Winter
Travel and culture	Continents, flags, Blackpool
Games and tasks	Board game, proverbs, colouring and doodling

A specially trained trial implementer (eg, nurse, therapist or researcher) will visit the dyad at home and provide therapy training to the companion. During the training session, the companion will receive the therapy manual, an activity resources pack, the therapy log (companion's diary), information related to the history and objectives of the therapy, and guidance on the nine core principles of the therapy. The trial implementer will guide the participant through a sample session, and the companion will be encouraged to continue with a short session afterwards. The trial implementer will provide constructive feedback to the companion after the session. Once the 10-week intervention period has started, the trial implementer will contact the companion weekly to confirm ongoing consent and adherence and to provide therapy support (if needed). In exceptional circumstances and where telephone assistance is not sufficient (eg, companion doubting confidence in their ability to continue delivering the training), further home visits may be made for ‘refresher’ training sessions. If the dyad is unable to complete any therapy for more than three successive weeks, they will be withdrawn from the trial. To standardise training, the trial implementer will follow a detailed training protocol.

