### ‘Treatment as usual’ (control) group

For the purposes of the feasibility evaluation, the inclusion of a control group (ie, TAU) is important because it allows for a more realistic evaluation of the operational aspects (ie, recruitment, retention and randomisation) as well as the implementation of the intervention.^23^ If conducted in an unblinded, non-randomised manner, the outcomes, particularly for a complex psychosocial intervention such as is being tested here, may be quite different. Furthermore, since previous evidence enabled us to power the primary outcome measure, cognitive function, for an evaluation of efficacy, a pilot trial was considered possible and this required inclusion of a control group to account for the natural progression of symptoms during the trial. Specifically, in the TAU comparator arm, dyads will not receive any additional intervention to their standard NHS treatment for PD and cognitive impairment or DLB. Typically, this involves dopamine replacement therapy for the symptomatic relief of Parkinsonism, cognitive enhancing medication (eg, cholinesterase inhibitors) and support from a Parkinson's disease nurse specialist. Since people with Parkinson's-related dementia tend to have significant symptoms in multiple domains, the support of occupational therapist, speech and language therapists and physiotherapists is often required. These interventions will be available to both the TAU as well as those dyads randomised to the active treatment arm. Treatment fidelity will be actively monitored in the control group, as it is in the experimental group, to ensure that the control group do not receive an active intervention component which could reduce the effect size between the experimental and control groups or, similarly, to ensure that an iatrogenic component is not added to the control group which could artificially inflate the difference in outcomes between the two groups.^24^

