#### Primary and exploratory outcome measures

The piloted efficacy and exploratory outcome measures for the participant are outlined in table 5a and the exploratory outcome measures for the companion in table 5b. The pilot efficacy measure on which the study has been powered is cognitive function as assessed using the Addenbrooke's Cognitive Examination III^26^ and the Everyday Cognition Questionnaire.^27^ Although the pilot trial has been powered on a previously reported effect size, the adaptation of the therapy and single outcome measure means that any potential treatment effects will be interpreted cautiously in order to not mislead the subsequent sample size and power calculation of the full RCT with multiple outcomes.^28^ With this caveat, we will test the hypothesis that compared with the TAU group, the difference in the total cognitive score between baseline and endpoint will be significantly greater in the experimental group. We will undertake a complete case analysis, only including trial completers without missing data, as well as an additional analysis based on last observation carried forward for dyads with missing data. Group differences in the change of outcome measures will be assessed using t-test or analysis of covariance adjusting for baseline differences, including cognitive stage at baseline.

**Table 5 T5:** Primary and exploratory outcome measures

Measure/author	Purpose	Time point

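### Dyads that lapse from therapy are withdrawn from the trial, a rule only CST-PD dyads can meet; neither the completer analysis nor LOCF repairs the resulting loss, so the cognition comparison may be biased

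*Protocol article*

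**What the plan says.** - **Withdrawal rule** (Active intervention): "If the dyad is unable to complete any therapy for more than three successive weeks, they will be withdrawn from the trial". The withdrawal is from the trial, not only from therapy.
- **Control arm** (Treatment as usual): "in the TAU comparator arm, dyads will not receive any additional intervention to their standard NHS treatment". No matching withdrawal rule is given for TAU.
- **Analysis sets** (Primary and exploratory outcome measures): "We will undertake a complete case analysis, only including trial completers without missing data". The same sentence adds a second analysis that uses LOCF where data are missing. The test is a t-test or ANCOVA on change, adjusting for baseline differences that include cognitive stage.
- **Timing** (Methods and Table 5): cognition is measured "when assessed at baseline and 12 weeks post-randomisation". Every outcome in Table 5 is taken at baseline and post-test only.
- **Status of the comparison**: Methods says "The pilot trial is designed and powered to test the hypothesis that CST-PD is superior to TAU". Objectives makes efficacy a secondary exploration, and the outcome section says effects will be read cautiously.
- **Feasibility measures** (Table 4): attrition is dyads withdrawn over dyads consented. Adherence is a separate measure, taken from the companion's session log.

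**The concern.** Meeting the rule is a post-randomisation event that can occur in one arm only, and it ends participation in the trial. As the article describes it, the outcome is then not collected, and no later analysis can recover it. The protocol itself points to participant frailty, fluctuating symptoms and companion responsibilities. Any of these could cause a lapse of more than three weeks and also accompany a worse 12-week score. If so, the CST-PD dyads left in the analysis are a favourable selection, and TAU undergoes no equivalent selection by this rule.

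Two uses of the trial are exposed. One is the estimate of the treatment effect, which feeds the decision on a larger trial. The other is the attrition rate, a primary feasibility outcome, which in CST-PD would partly measure the protocol's own rule and not whether dyads were willing to stay.

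**Working it through.** **Plan's own figures.** The sample size section says "have estimated the standardised effect size on cognition of the parent form of the intervention to be 0.4" and "assuming 80% power and a correlation coefficient of 0.5 between baseline and endpoint on cognitive outcomes, the required sample size is 27 completers per group". The attrition step reproduces: 27/0.85 = 31.8, so 32 per group. The 27 comes out within 2 of the total (26 per group, power 0.807) as a group-by-time test with f = 0.2, r = 0.5 and two-sided alpha of 0.05 (assumed). This point does not depend on that figure.

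**Inputs.** 32 per arm and r = 0.5 come from the protocol. The true effect is set to 0. The missing fractions and the correlation ρ between lapsing and a poor outcome are assumptions; the protocol gives neither.

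**Complete-case bias.** Suppose a fraction q of an arm is lost, being those lowest on a latent tendency that correlates ρ with the baseline-adjusted outcome residual. The mean of those remaining shifts upwards by

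shift = ρ × s × m(q), where m(q) = φ(z_q)/(1 − q)

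For ANCOVA, s = √(1 − 0.5²) = 0.866 SD. Values of m(q):
- q = 5%: 0.103/0.95 = 0.109
- q = 10%: 0.175/0.90 = 0.195
- q = 5/32 = 15.6%: 0.240/0.844 = 0.284
- q = 20%: 0.280/0.80 = 0.350
- q = 25%: 0.318/0.75 = 0.424

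Example, 25% against 5% with ρ = 0.5: 0.5 × 0.866 × 0.424 = +0.18 SD if TAU dropout is unrelated to outcome. If TAU dropout is equally related, subtract 0.5 × 0.866 × 0.109 = 0.05, which leaves +0.14 (simulation: +0.13).

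**Type I error.** Same example: SE = 0.866 × √(1/24 + 1/30.4) = 0.236, and 0.183/0.236 = 0.78. Then P(Z > 1.96 − 0.78) + P(Z < −1.96 − 0.78) = 0.118 + 0.003 = 12%.

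| Missing CST-PD / TAU | ρ | TAU dropout unrelated: bias, type I | TAU dropout equally related: bias, type I |
|---|---|---|---|
| any | 0 | 0, 5% | 0, 5% |
| 5 of 32 / 0 | 0.3 | +0.07, 6% | not applicable |
| 5 of 32 / 0 | 0.5 | +0.12, 8% | not applicable |
| 25% / 5% | 0.3 | +0.11, 7-8% | +0.08, 6% |
| 25% / 5% | 0.5 | +0.18, 12% | +0.14, 9% |
| 20% / 10% | 0.5 | +0.15, 10% | +0.07, 6% |

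Simulation of the same scenarios agrees to within about 0.01 SD and one percentage point. A t-test on change gives slightly larger values, because the SD of change is √(2 × (1 − 0.5)) = 1 and not 0.866. With 5 of 32 withdrawn it gives +0.08 (ρ = 0.3) and +0.14 (ρ = 0.5).

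**LOCF.** Baseline is the only earlier value, so each withdrawn dyad gets a change of 0. With no average change, the arm mean shifts by (1 − q) × ρ × m(q) = ρ × φ(z_q). For 5 of 32 and ρ = 0.5 this is 0.5 × 0.240 = +0.12, against +0.14 for completers. Simulated false-positive rates in favour of CST-PD are 7.3% (LOCF) and 7.9% (completers), against a nominal 2.5%. If untreated cognition declines by δ on average, LOCF adds a further q × δ in favour of CST-PD, even when ρ = 0.

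**Attrition.** Five rule-driven withdrawals would be 5/32 = 15.6% of the CST-PD arm. Alone they would use up the planned 15% allowance there (32 − 5 = 27).

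**The case against.** A reader might infer more than the text supports, in four ways.

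- **Completers as the main or only analysis.** The protocol does not call the complete-case analysis main, and the same sentence adds LOCF, which does retain withdrawn dyads. This is a fair correction, but LOCF here is baseline carried forward: it reduces the bias a little and does not remove it.
- **Adherent CST-PD dyads against all TAU dyads.** This is wrong on both sides. The rule needs more than three consecutive weeks with no therapy at all, so patchy adherers stay in. TAU dyads with missing data are also dropped.
- **Bias towards CST-PD as a fact.** The companion delivers the therapy, so a lapse may reflect the companion's circumstances and not the participant's cognition. At zero correlation complete-case bias is nil. Adjustment for baseline cognitive stage would absorb selection on baseline severity, and weekly contact and refresher visits aim to prevent lapses. The larger figures also need TAU dropout to be unrelated to outcome, and they charge all CST-PD missingness to this rule although some dyads would leave anyway.
- **Attrition hopelessly confounded with non-adherence.** Session logs are kept, so rule-driven withdrawals can be identified and reported apart.

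It is also fair that efficacy is secondary and exploratory, and that a condensed article may leave follow-up of withdrawn dyads to the full protocol. But the article fixes both withdrawal from the trial and a completers-only set. Even a dyad assessed after withdrawal would not be a trial completer.

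**Conclusion.** The concern holds as a possible bias, not a demonstrated one. The protocol contains a one-arm rule that removes dyads from the trial, a completer analysis, and an LOCF analysis that cannot repair the loss. Complete-case bias by ANCOVA runs from 0 to about +0.18 SD, at most 0.18/0.4 = 45% of the planning effect. Two-sided type I error runs from 5% to about 12%. These ranges rest on assumed missingness of 15-25% in CST-PD against 0-10% in TAU and correlations of 0 to 0.5; the top of each needs TAU dropout to be uninformative. With equally informative TAU dropout, the 25%/5% and 20%/10% scenarios at the non-zero correlations tabulated give about +0.07 to +0.14 SD and 6-9%. The direction is plausible from the protocol's account of frailty and companion burden, but nothing in it establishes the direction. The attrition rate is affected whatever the direction, because non-adherence enters it in one arm only. This should be corrected. It does not invalidate the feasibility aims, and no confirmatory claim rests on the comparison.

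**What to change.** 1. **Active intervention:** record a dyad meeting the rule as having discontinued therapy, keep it in the trial, and seek the blinded post-test unless consent is withdrawn. The rule on when therapy itself stops is left as it is.
2. **Primary and exploratory outcome measures:** name as the primary efficacy analysis one that includes every randomised dyad with a post-test, in its allocated arm, regardless of therapy received. Completers or adherers, and LOCF, become supportive analyses.
3. **Table 4:** report discontinuation of therapy separately from loss to follow-up, by arm.

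Cost: an amendment and a few more home visits. These are not trivial, since Table 5 lists 13 participant and 8 companion measures and the dyads concerned are already burdened. The protocol does not say whether those visits are funded. The estimated effect will be somewhat diluted by dyads that stopped therapy.
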